## Abstract

**Background:**

Myasthenia gravis (MG) is an acquired autoimmune disease with high heterogeneity. The disease is chronic, relapsing repeatedly and progressive with acute exacerbation occasionally. Although the treatment of MG has developed, it is still unsatisfactory and has some unexpected side effects. Traditional Chinese medicine (TCM) has shown great potential in MG treatment, including relief of muscle weakness syndrome, improvement of patient’s quality of life, and reduction of side effects of western medicine. The purpose of this study is to evaluate the effectiveness of modified Buzhong Yiqi decoction (MBYD) as an add-on therapy for MG through a small series of N-of-1 trials.

**Methods:**

Single-centre, randomized, double-blind, 3 crossover N-of-1 trials will be conducted to enroll patients with MG diagnosed as spleen-stomach deficiency syndrome or spleen-kidney deficiency syndrome in TCM. Each N-of-1 trial has 3 cycles of two 4-week periods containing the MBYD period and placebo period. The wash-out interval of 1 week is prior to switching each period. Primary outcome: quantitative myasthenia gravis (QMG). Secondary outcomes: the following scales: myasthenia gravis composite (MGC), myasthenia gravis activities of daily living profile (MG-ADL), myasthenia gravis quality of life (MG-QOL); the level of CD4+FoxP3+Treg cells and cytokines (IL-4, IL-17A, INF-γ, TGF-β) in the peripheral blood; the alterations of the composition of gut microbiota; reduction of the side effects of western medicine.

**Discussion:**

Used by WinBUGS software, we will conduct a hierarchical Bayesian statistical method to analyze the efficacy of MBYD in treating MG in individuals and populations. Some confounding variables such as TCM syndrome type and potential carryover effect of TCM will be introduced into the hierarchical Bayesian statistical method to improve the sensitivity and applicability of the trials, and the use of prior available information within the analysis may improve the sensitivity of the results of a series of N-of-1 trials, from both the individual and population level to study the efficacy of TCM syndrome differentiation. We assumed that this study would reveal that MBYD is effective for MG and provide robust evidence of the efficacy of TCM to treat MG.

**Trial registration:**

Chinese Clinical Trial Register, ID: ChiCTR2000040477, registration on 29 November 2020.

## Background

Myasthenia gravis (MG), characterized by weakness symptoms of various muscle groups, such as ptosis, dysphagia, dyspnea, limb weakness, and so on, is an antibody-mediated acquired autoimmune disease. The prevalence rate of MG ranges from 2.19 to 36.71 per 100,000, which depends on the geographic location [1]. Most MG patients (about 85%) have detectable antibodies against the acetylcholine receptor (AChR) in their serum [2]. It is a chronic, progressive, and stubborn neuromuscular disease that seriously affects MG patients’ quality of life.

The pathogenesis of MG has not entirely cleared. However, it was determined that it is highly correlated to immune dysregulation. CD4+T cells and their cytokines play a crucial role in the development and the progress of MG. CD4+ Foxp3+ regulatory T (Treg) cells, which are responsible for suppressing the immune response [3], have a protective pole in MG. Inflammatory cytokines such as interferon(IFN)-γ and interleukin(IL)-17 increase the anti-AChR level and aggravate MG weakness symptoms while anti-inflammatory cytokines such as transforming growth factor(TGF)-β and IL-4 downregulate anti-AChR level and alleviate weakness symptom [4, 5].

On the other hand, with the development of metagenomics, metabolomics, metatranscriptomics, and other omics, gut microbiota has attracted more and more attention and become an important frontier in understanding the development and progression of diseases [6]. In recent years, studies revealed that gut microbiota in MG patients has lower biodiversity and a lower *Firmicutes*/*Bacteroidetes* ratio as well as a significantly lower *Clostridium* content than that in healthy people. The disorder of gut microbiota promotes immune inflammation response, which aggravates the severity of MG [7, 8].

MG is usually treated with conventional western medicine such as acetylcholinesterase inhibitors, glucocorticoid, and other non-steroidal immunosuppressants with dissatisfactory clinical effects in some patients, the risk of unconscionable dosage, and unwanted adverse effects where traditional Chinese medicine (TCM) can take a complementary and alternative effect. A study found that using TCM combined with western medicine might improve the total effect and reduce the risk of MG relapse [9]. According to the TCM characteristic theory of “spleen governing muscle,” MG is generally diagnosed as “spleen *qi* deficiency syndrome” and thereby, strengthening the spleen and replenishing *qi* is a common therapeutic strategy of MG in TCM, which has played a positive role in clinical practice of MG [10, 11]. Buzhong Yiqi decoction (BYD), a classical *qi*-supplementing formula in TCM, is the most frequently used prescription to treat MG. A study showed that BYD modulated the balance of Treg and Th17 cells in patients with MG and downregulated the serum AChR antibody level [12]. Modified BYD (MBYD) is based on BYD and adds other Chinese herbs to treat MG patients’ specific or concurrent symptoms synergistically. A pharmacological study demonstrated that *Huangqi*, *Wuzhimaotao*, and *Gancao,* which are all in MBYD, have pharmacological components of acetylcholinesterase inhibitors [13]. Several clinical observations demonstrated that treating MG by combining MBYD with western medicine is more effective than western medicine alone [14–16]. However, high-level evidence of the effectiveness of MBYD for treating MG has yet to be constituted.

In this study, we will detect the level of Treg cells in the peripheral blood by flow cytometry and cytokines (IL-4, IL-17A, INF-γ, TGF-β) in serum by ELISA to investigate how MBYD modulates immunoregulatory cells and cytokines. What is more, studies have found that TCM contains complex compounds that, after taken orally, will inevitably interact with gut microbiota and modulate the structure and metabolism of gut microbiota and thereby obtain their therapeutic effects [17, 18]. We innovated to investigate the alterations of gut microbiota after TCM treatment in N-of-1 trials. This method has not been reported in previous studies. We collected stool samples from MG patients at baseline and after each cycle to determine the changes of the gut microbiota with MBYD treatment through multiple cross-controls.

### The rationales for the trials

Considering MG is a rare disease with high heterogeneity, conventional large-scale RCT trials are challenging to carry out. Single-case of the randomized controlled trial (also called “N-of-1”) is a multiple-crossover, two-phase cross design in a single patient to compare the efficacy of two interventions (or an intervention and a placebo), which requires an exceedingly smaller sample size than RCT [19]. There are some reasons why we will conduct this trial:
N-of-1 trials provide the most rigorous evidence possible of the effectiveness of the intervention in the individuals by multiple-crossover randomized controls [20]. Therefore, evidence from several N-of-1 trials can be gathered to create the efficacy estimates of the population treatment.N-of-1 trials are fit for chronic, nonself-limited, relatively stable diseases requiring long-term medication treatment. Therefore, we set a rule that participants should have a stable phase in MG for at least 3 months.TCM is characterized by syndrome differentiation and individualized intervention. N-of-1 trials can design various intervention measures flexibly for individuals. Hence, this method is relevant to the clinical practice of TCM. Nowadays, TCM N-of-1 trials, as the most compatible clinical method with TCM clinical diagnosis and treatment, have been widely concerned [21–23].

### Objectives

In this study, our objective is to comprehensively evaluate the effectiveness of MBYD in the treatment of MG. We assumed that this study would provide a credible conclusion that MBYD is an effective prescription for MG, which alleviates clinical symptoms, enhances the quality of life of MG patients, and reduces the side effects of western medicine. Furthermore, this study investigated the alterations of the level of Treg cells and cytokines (IL-4, IL-17A, TGF-β, IFN-γ) in peripheral blood and the gut microbiota in the intestinal tract of MG patients at baseline and after each phase so as to preliminarily explore how MBYD effects the immune system and gut microbiota in MG patients.

## Method

### Trial design

Because of the heterogeneous components of Chinese herbs, the onset time and half-time of Chinese herbs are hard to confirm [24]. According to previous clinical observation and preliminary trial [11], we decided to set the intervention period or control period for 4 weeks and the wash-out interval for 1 week. Each cycle comprises a 4-week intervention period with MBYD combining conventional western medicine and a 4-week control period with placebo with the same western medicine in random order. The wash-out interval prior to switching each period makes carryover effects minimized. Hence, there are 29 weeks in all involving 3 cycles in this study (Fig. 1). The conventional western medicine that the patients take still follows his/her original therapeutic schedule. In view that patients with MG cannot stop taking conventional western medicine for a few days, which may aggravate their condition rapidly and lead to serious adverse events, only MBYD or placebo granules are washed out while western medicine is maintained during the wash-out interval. The protocol is conducted in light of the SPIRIT reporting guidelines [25] and obeys the Conventional Protocol Items: CONSORT extension for reporting N-of-1 trials (CENT) 2015 and CONSORT extension for reporting N-of-1 trials for traditional Chinese medicine (CENT for TCM) 2019 [24, 26]. Table 1 shows the schedule of enrolment, interventions, and outcomes and safety assessments.

**Fig. 1 Fig1:**
[figure not shown]
Design of the study. **A** is for the MBYD period. **B** is for the placeno period. **W** is for the wash-out interval. The order **A** and **B** in each cycle will be randomized. Figure not to scale

**Table 1 Tab1:** Schedule of enrolment, interventions, outcomes, and safety assessments

Time point		Enrolment	Allocation	Cycle1		Cycle2		Cycle3		Close-out
				Weeks 1–4	Weeks 6–9	Weeks 11–14	Weeks 16–19	Weeks 21–24	Weeks 26–29	
Enrolment	Eligibility screen	√								
	Informed consent	√								
	Allocation		√							
Intervention	MBYD granules or placebo with the conventional western medicine			√	√	√	√	√	√	
Outcome	QMG score	√		√	√	√	√	√	√	√
	TCM syndrome score; MGC; MG-ADL; MG-QOL	√		√	√	√	√	√	√	√
	The level of CD4+ Foxp3+ Treg cells and cytokines (IL-4, IL-17A, INF-γ, TGF-β)	√		√	√	√	√	√	√	
	Gut microbiota	√		√	√	√	√	√	√	
Safety assessment	Laboratory tests	√		√	√	√	√	√	√	√
	Vital signs	√		√	√	√	√	√	√	√
	Adverse events	√		√	√	√	√	√	√	√

### Recruitment

The First Affiliated Hospital of Guangzhou University of Chinese Medicine (GZUCM) that we conduct the study is one of the centers for MG treatment in China and lots of MG patients will come to visit. Patients will be recruited as the participants from outpatient or resident physicians who professionally treat MG in GZUCM.

The patients will be selected if they adapt to the inclusion criteria as follows:
Patients aged between 18 and 65 and gender are not limitedPatients diagnosed with MG based on “The Chinese guidelines for the diagnosis and treatment of myasthenia gravis (2020)”: patients with typical clinical features of MG (fluctuating myasthenia) excluded from other diseases and meeting any of the following three points, including pharmacological examination, electrophysiological characteristics or serum antibody detection [27]Patients attached to the spleen-stomach deficiency syndrome or spleen-kidney deficiency syndrome will be enrolled which is based on “The guidelines for clinical diagnosis and treatment of internal medicine of traditional Chinese Medicine: myasthenia gravis (2020)” [28]Patients identified as class II or III according to myasthenia gravis foundation of America (MGFA) clinical classification [29] and are in the stable stage of MG at least 3 monthsPatients with Quantitative Myasthenia Gravis (QMG) score more than 6Patients treated with glucocorticoid administration should not take more than 15 mg prednisone (or an equivalent dose of other glucocorticoids) per day.

The exclusion criteria are following:
Female patients who are pregnant or lactating or have a pregnancy plan during the trialPatients with other autoimmune diseases (e.g., polymyositis, multiple sclerosis, rheumatoid arthritis) that may impact the assessment and treatmentPatients with severe heart, kidney, liver, lung, hematological system, infectious diseases, or cancerPatients with neuropsychiatric disorders that cannot cooperatePatients received plasma exchange, glucocorticoid, or gamma-globin pulse therapy within 3 monthsPatients received thymectomy within half a yearPatients with hypersensitivity of any drug in this trialPatients participating in other trialsPatients consumed antibiotics, probiotics, or anti-acids during the previous 2 months

The withdrawal criteria are following:
Patients with poor adherence and not taking the trial medication as required by the study protocolPatients who are allergic to the trial medication.Patients with serious adverse effect (SAE) or suspected unexpected serious adverse reaction (SUSAR)Patients with myasthenic crisis or worsening of symptoms requiring any treatment other than the trial medicationPatients who decide to withdraw from the trial or lose follow-up

The finished cycles before the withdrawal will be analyzed as part of the trial. We will still follow up with withdrawn participants until their planned end in order to appraise any adverse effects of the trial medication.

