### Interventions

In consideration of the hardship in guaranteeing the quality of the decoction, we intend to use granules in this study. The conventional western medicine administration such as pyridostigmine, low-dose prednisone, and immunosuppressants is in the light of their prestudy treatment schedule. In order to avoid the effects of other Chinese herbs, any drug containing ingredients from Chinese herbs is not allowed except MBYD. Moreover, patients are not allowed to take antibiotics, probiotics, or anti-acids, which can obviously affect gut microbiota during the trial. For patients who develop an infection that requires antibiotics during the trials, they will suspend the cycle until symptoms resolve and antibiotics have been discontinued for 2 months, which is the time for the recovery of gut microbiota after antibiotics shown by the animal study [30]. After then, they will restart that cycle from the beginning.

The MBYD consists of *Astragalus Membranaceus* (*Huangqi*), *Radix Fici Simplicissimae* (*Wuzhimaotao*), *Rhizoma Atractylodis Macrocephalae* (*Baizhu*), *Radix Codonopsitis* (*Dangshen*)*, Poria Cocos* (*Fuling*), *Radix Bupleuri* (*Chaihu*), *Cimicifuga Foetida* (*Shengma*), *Pericarpium Citri Reticulatae* (*Chenpi*), *Angelica Sinensis* (*Danggui*), *Semen Coicis* (*Yiyiren*), *Rhizoma Dioscoreae* (*Shanyao*), *Radix Liquiritiae* (*Gancao*), and *Radix Scrophulariae* (*Xuanshen*). Patients with MG who have spleen *qi*-deficiency syndromes and kidney deficiency syndromes are usually diagnosed with spleen-kidney deficiency syndrome according to TCM theory and in that case, *Morinda officinalis* (*Bajitian*), *Cistanche Salsa* (*Roucongrong*), *Semen Cuscutae* (*Tusizi*), *Cornus Officinalis* (*Shanzhuyu*), *Taxillus sutchuenensis Danser* (*Sangjisheng*), and *Rosa laevigata Michx* (*Jinyingzi*), which are together used to replenish kidney *qi*, will be added in MBYD. Both the MBYD granules and the placebo granules were manufactured by Guangdong Yifang Pharmaceutical Co. Ltd.(10 g/bag, 2 bags three times a day, last number: J2004021). The placebo granules were identical to the MBYD granules in appearance, texture, color, and odor.

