### Outcomes

Given the multi-component and multi-target characterization of TCM, an all-round assessment of its effective evaluation is significant. In this study, the primary outcome is the QMG score. The QMG score will be assessed by a physician with experience in MG according to the MGFA manual [29]. The QMG score has 13 items with 0–3 points for each item and a total score of 0–39 points. A higher QMG score indicates a more severe disease condition, and a decrease of 2.6 points is considered to be of clinical significance [31]. The secondary outcomes are the following:
TCM syndrome score. Assessing TCM syndrome score is based on “Diagnosis standards for common syndromes in traditional Chinese medicine” [32] issued by the Chinese Medicine Diagnostic Branch of China Association of Traditional Chinese Medicine. The measurement information of each symptom and sign of MG patient are weighted and summed according to the values of different symptoms and signs.The scores of the following scales: myasthenia gravis composite (MGC), myasthenia gravis activities of daily living profile (MG-ADL), myasthenia gravis quality of life (MG-QOL)The level of CD4+ Foxp3+ Treg cells and cytokines (IL-4, IL-17A, INF-γ, TGF-β) in the peripheral bloodThe alteration of gut microbiota. Before the trials begin and after each period, we will collect the patients’ fresh fecal samples and then immediately store them in the laboratory freezer at − 80 °C until analyses. We will analyze the gut microbiota in the stool samples in order to explore the mechanism of MBYD in MG therapy at the microbiological level by the 16S rRNA gene sequencing.The reduction and alleviation of side effects of western medicine for MG treatment

The safety assessments consist of the following items:
Laboratory tests, including serum alanine aminotransferase, aspartate aminotransferase, urea nitrogen, creatinine, and routine blood testsVital signs, physical examination, and electrocardiographAdverse events occurring during the study, including MG crisis, drug allergy, hepatorenal insufficiency, and other adverse drug reactions

The outcomes and the safety assessments will be conducted before the trials begin and at the end of each period.

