### Sample size

We conducted the preliminary trials that 3 patients had finished all the three cycles. The mean and standard deviation (SD) of QMG scores (the primary outcome) difference between MBYD and placebo groups was (3.00±1.94). The sample size calculation was based on the effect of treatment with QMG scores [19]. We assumed that there were differences in treatment effect among different patients, and the difference value(Ψ) was 3.0. We used the two-sided test and set the type I error α of hypothesis test as 0.05 and the error β of class II as 0.2. Based on the estimate assuming 3 cycles, the sample size was calculated as 13 (random model) by using R 4.0 software [33–35]. Considering the 20% of lost follow-up rate, we set the sample size as 17.

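### Withdrawal is triggered by worsening, and the cycles finished before withdrawal are named as what is analysed, so the QMG comparison may lose the periods that ended in treatment failure

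*Protocol article*

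**What the plan says.** All references are to the protocol article.

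- **Recruitment, withdrawal criteria.** Grounds for withdrawal include poor adherence, allergy to the trial medication, crisis or worsening that calls for other treatment, and "Patients with serious adverse effect (SAE) or suspected unexpected serious adverse reaction (SUSAR").
- **Recruitment, closing paragraph.** For withdrawn patients the rule on data is: "The finished cycles before the withdrawal will be analyzed as part of the trial". Follow-up continues, with a safety purpose: "We will still follow up with withdrawn participants until their planned end in order to appraise any adverse effects of the trial medication".
- **Outcomes.** "In this study, the primary outcome is the QMG score", with higher scores meaning worse disease. On timing: "The outcomes and the safety assessments will be conducted before the trials begin and at the end of each period".
- **Interventions.** A patient who needs antibiotics suspends the cycle until symptoms resolve and antibiotics have been stopped for 2 months. Then: "After then, they will restart that cycle from the beginning".
- **Sample size.** The pilot result is given as "The mean and standard deviation (SD) of QMG scores (the primary outcome) difference between MBYD and placebo groups was (3.00±1.94"). The section assumes that the treatment effect differs between patients, with "the difference value(Ψ) was 3.0". It arrives at 13 patients under a random model with 3 cycles, raised to 17 for 20% loss.

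**The concern.** Crisis and worsening are what QMG is meant to measure. A rule that ends participation on worsening and then analyses finished cycles selects data after randomisation on something close to the primary outcome. The failing period has no scheduled QMG score, because scores are taken at period ends, and the rest of its cycle goes with it.

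Two routes lead to bias. First, worsening may be more frequent in one type of period; the arm with more failures then looks better than it is. Second, patients who do badly on MBYD may leave early, so that those who respond well supply most of the finished cycles. The protocol's own assumption of different effects in different patients makes the second route a live one.

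Neither the 20% allowance nor the model in Statistical methods deals with this. The allowance replaces numbers without restoring comparability. The model as described does not bring truncated cycles, or worsening itself, into the QMG analysis.

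**Working it through.** **1. What each kind of withdrawal leaves in the analysis, on the natural reading**

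| Event | Failing period | Other period of that cycle | Earlier cycles |
|---|---|---|---|
| Worsening in first period of cycle 1 | no score | never takes place | none exist |
| Worsening in second period of cycle 1 | no score | completed, not used | none exist |
| Worsening in cycle 2 or 3 | no score | not used, even if completed | used |
| Poor QMG at the end of a period, cycle finished | used | used | used |

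The loss is thus confined to worsening that leads to withdrawal before a cycle is finished.

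**2. The plan's own sample size, to obtain a suitable standard error**

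Inputs from Sample size: difference 3.0, Ψ = 3.0 (read as the between-patient SD of the effect), 1.94 (read as the within-patient SD), 3 cycles, two-sided α 0.05, power 0.80.

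- Variance of a patient's mean difference = Ψ² + 2σ²/k = 3.0² + 2 × 1.94²/3 = 9 + 2.51 = 11.51, so the SD is 3.39.
- With the noncentral t distribution, power is 0.796 at n = 12 and 0.833 at n = 13. The smallest n reaching 0.80 is 13, as stated.
- 13/0.8 = 16.25, rounded up to 17, as stated.
- Standard error with 13 patients = 3.39/√13 = 0.94.

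The sample size is not at fault. It supplies the yardstick.

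**3. An illustrative size**

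The documents give no rate of withdrawal for worsening. As an extreme case, let the whole 20% loss be worsening, all in one arm. Each patient has three periods on that arm, so the risk p per period solves 1 − (1 − p)³ = 0.20:

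- p = 1 − 0.8^(1/3) = 0.072.
- Missed effect = (p in one arm − p in the other) × QMG rise. The rise of 3 to 6 points is an assumption.
- 0.072 × 3 = 0.22 points; 0.072 × 6 = 0.43 points.
- Against the standard error: 0.22/0.94 = 0.23 and 0.43/0.94 = 0.46.

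If the failures are all in MBYD periods, this much harm is missed. If all are in placebo periods, the same amount of benefit is missed. Any split between arms makes the figure smaller.

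**4. Direction**

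A simulation of the mechanism (200,000 patients per scenario) withdrew a patient when a period ended 2.0 to 2.6 points above baseline and dropped that whole cycle.

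| True mean benefit | Ψ | Estimate from finished cycles |
|---|---|---|
| 0 | 0 | about 0 |
| 0 | 3.0 | 1.31 to 1.51 in favour of MBYD |
| 3 | 0 | 2.49 to 2.90 |

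The second row overstates the benefit and the third understates it. The use made of this is limited to direction, for the reasons given under the objection.

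**The case against.** **'Only' is an inference.** The sentence in Recruitment can be read as an inclusion rule that protects the completed cycles of withdrawn patients. It does not say that a completed first period is discarded, and an analysis plan that is not shown may say more. This stands as a caution. But the sentence names finished cycles as what is analysed, and the next one gives later follow-up a safety purpose alone. Exclusion of partial cycles is therefore the natural reading, and the ambiguity itself needs removing.

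**The worst outcomes are not removed wholesale.** A reader might infer that treatment failure disappears from the trial. It does not: poor scores in finished cycles remain, crises are recorded as adverse events, and withdrawn patients are followed to their planned end.

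**The antibiotic restart is a different matter.** A reader might group it with withdrawal for worsening. Its trigger is infection needing antibiotics, not QMG; the microbiota reason is given for the 2-month wait; and nothing says that earlier scores are deleted. The documents do not show a selection on outcome here. What remains is a possible loss of valid first-period QMG scores.

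**Larger sizes are tempting but unsupported.** Dividing 0.43 by 1.94/√13 = 0.54 gives about 0.8 of a standard error, but this leaves out the between-patient variation that the protocol assumes. With it, the ratio is 0.46. The simulated shift of 1.3 to 1.5 points is no estimate for this trial either. It replaces the protocol's trigger with a QMG threshold and withdraws patients in 31 to 39% of MBYD periods. It leaves 24 to 40% of patients without a finished cycle, against a planned loss of 20%. It also drops cycles whose second period had ended with a score, and it pools cycles instead of fitting the hierarchical model.

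**Conclusion.** The concern holds and should be fixed. As written, the rule lets worsening decide which periods enter the primary comparison, and nothing in Outcomes, Sample size or Statistical methods repairs this. The bias is near zero if worsening is unrelated to treatment and patients respond alike; the protocol assumes that they do not respond alike. Its direction cannot be known in advance, so the documents do not support saying that the rule favours MBYD.

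The illustrative size is 0.22 to 0.43 points, or 0.23 to 0.46 of a standard error of 0.94. It rests on three assumptions that the documents do not supply: that all of the 20% loss is worsening, that all of it falls in one arm, and that QMG rises by 3 to 6 points. It also rests on reading Ψ and 1.94 in the way that reproduces 13 patients. Without a documented worsening rate, the size does not justify calling the flaw decisive.

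**What to change.** - In the primary analysis, fit the hierarchical model at period level to every period with a QMG score, as randomised. Include the completed first period of an unfinished cycle and the periods of poorly adherent patients.
- Score QMG when withdrawal or other treatment is decided, and use that score as the period's outcome. Add a sensitivity analysis with a worst-case value.
- Report the analysis of finished cycles only as a sensitivity analysis.
- As a secondary point, state that any end-of-period QMG obtained before an antibiotic-interrupted cycle is restarted stays in the QMG analysis.

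**Cost.** One unscheduled QMG assessment per withdrawn patient, since the article schedules no outcome visit at withdrawal, and a little more analysis. A score not taken at that moment cannot be recovered later. The estimate may move in either direction. No change to the clinical withdrawal criteria is needed or proposed.
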